### Secondary Study Outcomes

We will examine whether the intervention also improves the proportion of women providing valid vaginal samples and the proportion of women with invalid HPVss tests who repeat HPVss. We will also compare the detection rate of cervical intraepithelial neoplasia grade 2+ in the 2 groups. Median intervals between the date of the reminder letter and the date of the HPVss test report, and between the dates of sending a positive HPV test result and performing liquid-based cytology will be compared between groups, stratified by age group, place of residence, and health insurance type.

An evaluation of cost-effectiveness will also be performed, to first estimate the cost of the intervention and to calculate the incremental cost-effectiveness ratios as the mean difference in total costs between the intervention and control groups with the mean difference in effects, and expressed as both Euros and US dollars per percentage change in screening participation. Deterministic and probabilistic sensitivity analyses will also be conducted by varying key parameters that may affect the outcome and conclusions of the economic evaluation.

Women’s use of the chatbot will also be assessed through usage and engagement statistics generated by chatbot platforms. We will estimate the average number of messages each participating woman exchanged with the chatbot, the average interaction time spent by each participant and a session-wise split of duration, the average number of failed messages that the Chatbot failed to respond, the most frequently asked questions, and the language most often used to seek information, etc.

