### Objectives and Endpoints

The primary objective of this AppDate-You study is to assess the effectiveness of a chatbot-based decision aid to improve women’s participation in the HPVss detection–based CCS care pathway, in particular among noncompliant women living in disadvantaged areas in Occitanie Region, France.

The main secondary objectives are to evaluate the impact of the intervention on (1) the detection rate of cervical intraepithelial neoplasia grade 2+, (2) the intervals between the dates of the reminder letter and the HPVss test report and between the dates of sending a positive HPV test result and performing liquid-based cervical cytology (triage test), and (3) the efficiency (cost-effectiveness) of the intervention.

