### Statistical Analysis

The participants’ categorical characteristics will be presented as proportions compared between the intervention and control groups using chi-square analysis. Continuous variables will be presented as median (interquartile range) values. Comparisons will be carried out using Kruskal-Wallis tests. The effect of the intervention on both the primary and secondary outcomes will be assessed using logistic regression models, adjusting for individual characteristics that are statistically significant in the univariate analysis and the cluster design. The effect estimates obtained from the regression analysis will be presented as odds ratios together with their 95% CIs. Just Another Gibbs Sampler software will also be used to model missing data in outcomes and/or explanatory variables [31].

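### The interval outcomes are assigned a model that cannot estimate them, and the letter-to-report median compares arms among women selected by the outcome the chatbot is meant to change

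*Protocol article*

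**What the plan says.** All references are to the protocol article.

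- **Objectives and Endpoints** lists "the intervals between the dates of the reminder letter and the HPVss test report" among the main secondary objectives, together with the interval from sending a positive result to triage cytology.
- **Secondary Study Outcomes** sets the comparison. It names "Median intervals between the date of the reminder letter and the date of the HPVss test report" and says that the interval "between the dates of sending a positive HPV test result and performing liquid-based cytology will be compared between groups". Strata are age group, residence and insurance type.
- **Statistical Analysis** states: "The effect of the intervention on both the primary and secondary outcomes will be assessed using logistic regression models". It describes these models as "adjusting for individual characteristics that are statistically significant in the univariate analysis and the cluster design". The estimates are "presented as odds ratios together with their 95% CIs".
- The only method named for continuous variables is in the same section: "Comparisons will be carried out using Kruskal-Wallis tests". This sentence follows the description of participant characteristics and has no cluster term.
- On incomplete data, the section says that the Gibbs sampler software "will also be used to model missing data in outcomes and/or explanatory variables".

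The article states no denominator, censoring rule or time-to-event method for either interval.

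**The concern.** There are two separate problems.

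**The model does not fit the outcome.** An odds ratio compares the odds of a yes/no event. It is not an estimate of a difference between two median intervals. The outcome section and the analysis section therefore do not fit together for this objective.

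**The comparison is selected on a post-randomization outcome.** A letter-to-report interval has an end date only if the woman returned a self-sample and a report was issued. Participation is the first primary outcome, so the share of women with an interval is close to what the intervention is meant to change. Randomization does not make the two sets of testers comparable. If the chatbot brings in women who would otherwise not have tested, their timing enters one arm's median only. A chatbot that works could be reported as slowing screening, or as speeding it up, with no change in anyone's timing.

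The second interval has the same structure. HPVss-positive women are a post-randomization subset, and only those who had cytology have an end date. Recruitment runs from January 2023 to December 2024, with follow-up of positive women ending 12 months after the last recruitment, so observation time may also differ between women.

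**Working it through.** The article gives no figure for the interval outcomes, so there is nothing to reproduce. The checks below show the mechanism and its possible size.

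**Inputs from the article**
- Under 20% of non-compliant women self-sampled when mailed a kit (Introduction).
- Well-managed proportion 15% in control, with an expected gain of 10 points (Sample Size). This composite requires a valid self-sample and completed management, so here it is only a proxy for testing.
- 250 eligible women per cluster and 16 clusters per arm (Sample Size). The abstract's approximate 4000 women could be per arm (16 × 250 = 4000) or in total (4000 / 32 = 125 per cluster).
- Intracluster correlation (ICC) 0.029, stated for the binary outcome only.

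**Inputs assumed**
- Lognormal times to report with log-SD 0.6.
- Women who would test anyway have a median of 45 days in both arms. The chatbot delays nobody and only adds testers.

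**1. Who has an interval.** With the proxy, 100 − 15 = 85% of control women and 100 − 25 = 75% of intervention women have no interval. With fewer than half testing, a median over all recalled women would not be reached.

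**2. Median among testers.** In the intervention arm 15/25 = 0.6 of testers are the same kind of women as in control and 10/25 = 0.4 are added. For added testers with median M, the arm's median t solves

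0.6·Φ(ln(t/45)/0.6) + 0.4·Φ(ln(t/M)/0.6) = 0.5.

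Check for M = 90 and t = 59: 0.6 × 0.674 + 0.4 × 0.241 = 0.404 + 0.096 = 0.50.

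The proportion of all women tested by day 90 is 0.15·Φ(ln(90/45)/0.6) = 0.15 × 0.876 = 13.1% in control, and 13.1% + 0.10·Φ(ln(90/M)/0.6) in the intervention arm.

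| Median of added testers (days) | Tester median, control | Tester median, intervention | All women tested by day 90, control vs intervention |
|---|---|---|---|
| 30 | 45 | 38.3 | 13.1% vs 22.8% |
| 45 | 45 | 45 | 13.1% vs 21.9% |
| 60 | 45 | 50.5 | 13.1% vs 20.6% |
| 90 | 45 | 59 | 13.1% vs 18.1% |
| 120 | 45 | 65 | 13.1% vs 16.3% |

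By construction, cumulative testing is never lower with the chatbot on any day. With 15% versus 20% testing, added testers at 60, 90 and 120 days give intervention medians of 48.3, 52.8 and 55.2 days. In simulation with 4000 independent women per arm and 15% versus 25%, Kruskal-Wallis rejected in 93 to 100% of trials for added testers at 60 to 120 days, and in about 6% when timing was equal.

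**3. Level of Kruskal-Wallis if applied to the intervals.** Under no effect, testers per cluster are 250 × 0.15 ≈ 38, or 125 × 0.15 ≈ 19. Simulation used 16 equal-sized clusters per arm and a nominal 5% level:

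| Assumed ICC of the interval | 38 testers per cluster | 19 testers per cluster |
|---|---|---|
| 0.01 | 9% | 7% |
| 0.029 | 17% | 12% |
| 0.05 | 23% | 14% |

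Analytic check at 38 testers and 0.029: design effect 1 + 37 × 0.029 = 2.07, and 2·(1 − Φ(1.96/√2.07)) ≈ 0.17.

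**4. Would a hazard ratio summarise the effect?** For M = 90, the ratio of cumulative proportions is 4.1/3.7 ≈ 1.1 at day 30, 18.1/13.1 ≈ 1.4 at day 90 and 25/15 ≈ 1.7 once all have tested. With proportions this small, proportional hazards would keep the ratio nearly constant, so here they fail.

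**The case against.** **The denominator is inferred.** The article nowhere says that women without a report are dropped, and articles often leave denominators and censoring rules to the full protocol or SAP. This stands in part: a reader might infer that the plan states such a rule, and it does not. For the first interval, however, no other reading yields a median when fewer than half of women test. For the second, a median over all positive women could be reached, since the Introduction reports follow-up compliance of 41% and 92% in two studies. The point there is weaker. The mismatch between outcome and model is not left to another document, because the article fixes both.

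**Kruskal-Wallis may be only for baseline description.** Its position in the text favours this. A reader might infer that the intervals will be tested without regard to clustering; the article does not establish that. If the sentence covers baseline only, the inflated level falls away. Logistic regression, which does account for clustering, is then the only stated effect analysis and still cannot compare medians.

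**The size and direction are assumed.** This stands. A reader might infer that the chatbot will appear to slow screening. The documents give no timing data. Equal timing gives no shift, and earlier added testers shorten the median. Nor are 15% and 25% testing proportions.

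**Time to test in all women overlaps with the first primary outcome.** It does at 12 months. The time course before 12 months is extra information, and it keeps the randomized comparison. Medians among testers remain useful as programme indicators.

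**Conclusion.** The point holds for a main secondary objective. Two parts rest on the text with little inference: the stated effect model cannot estimate the stated interval comparison, and a letter-to-report median is in practice confined to a minority whose make-up the intervention is meant to change. Such a comparison can show a delay or a speed-up when no woman's timing has changed. Under the assumed timings, with 15% versus 25% as proxy testing rates, the apparent shift runs from about 7 days shorter (45 − 38.3) to 20 days longer (65 − 45).

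The clustering part is conditional. Only if Kruskal-Wallis is applied to the intervals is the level roughly 7 to 23% instead of 5%, for assumed ICCs of 0.01 to 0.05, 19 to 38 testers per cluster and equal cluster sizes. The primary conclusions do not depend on any of this.

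**What to change.** 1. Restrict the logistic regression sentence to binary outcomes, and say whether Kruskal-Wallis is for baseline description only.
2. Analyse time from reminder letter to HPVss report in all recalled women, censored at 12 months. Study Procedures also allows a clinician-collected test, so either treat that test as a competing event or declare any HPV test as the endpoint. The choice changes the outcome and should be explicit.
3. Report cumulative incidence by arm at fixed times with cluster-robust confidence intervals. Any Cox hazard ratio should use cluster-robust variance and be supplementary, because proportional hazards may fail.
4. Analyse time from positive result to cytology in all HPVss-positive women, censored at end of follow-up. Label it descriptive, because it conditions on a positive test after randomization.
5. Keep medians among women with a report, if wanted, as descriptive programme indicators.
6. State that a woman with no report by the end of observation is censored, not a missing value to be imputed.

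The cost is wording and a little more analysis work. The planned intervals already need the event dates, and a clinician-collected HPV test would need its date too. No change to the sample size or conduct of the trial follows.

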### Statistical Analysis

The participants’ categorical characteristics will be presented as proportions compared between the intervention and control groups using chi-square analysis. Continuous variables will be presented as median (interquartile range) values. Comparisons will be carried out using Kruskal-Wallis tests. The effect of the intervention on both the primary and secondary outcomes will be assessed using logistic regression models, adjusting for individual characteristics that are statistically significant in the univariate analysis and the cluster design. The effect estimates obtained from the regression analysis will be presented as odds ratios together with their 95% CIs. Just Another Gibbs Sampler software will also be used to model missing data in outcomes and/or explanatory variables [31].

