### Study Population

Eligible women are those aged 30-65 years who did not respond to an initial invitation letter to have an HPV test collected by a clinician, have not been screened for CC for more than 4 years, and live in the disadvantaged clusters in the Occitanie Region.

Women will be excluded from the study if they have undergone CC screening within the past 4 years, have had a hysterectomy, or have been diagnosed with and are receiving treatment for precancer or CC.

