### Sample Size

The sample size involved estimation of the number of clusters (IRIS) using a composite outcome, “well-managed” women, which is defined as those women who completed a valid HPVss test and were either advised of a negative result (in the case of HPVss-negative women) or completed the assessment (in the case of HPVss-positive women), and, where necessary, treatment pathway. The following assumptions were considered:

Expected average cluster size of 250 eligible women; this is an estimate of the number of women in the target age range (30-65 years) within a cluster of 2000 people, based on the population pyramid of ages in the Occitanie Region.Expected proportion of overall well-managed women in the control group of 15%.Expected absolute increase of 10% in the proportion of overall well-managed women in the experimental group.Coefficient of variation taking into account the possibility of varying cluster sizes of 1.2 (arrived at because of the wide level of dispersion around the mean cluster size) [26].A 10% precision in the proportion of overall well-managed women, which would lead to a 0.029 intracluster correlation using a beta-binomial model [27].A power of 80% and a 5% 2-tailed significance level.

Under the aforementioned assumptions, the required number of clusters to randomize in each arm would be 10 (total: 20 clusters). However, if subgroup analyses are to be performed, stratifying on general population density, medical density of the department (high or low), and setting of the community (rural or urban), taking into consideration these α adjustments (α=.3125% [2.5%/8]) for each of the subgroup analyses in order to be able to remain with a 5% 2-tailed significance level for the overall effect, approximately 16 clusters in each arm (32 clusters in total) will be required for the subgroup analyses.

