### Randomization

A sampling frame of a list of disadvantaged clusters was obtained from Caen University, Caen, France. Clusters (IRIS) will be randomly assigned to the 2 randomization groups in a 1:1 ratio using computer-generated simple randomization. Eligible women living in the randomly selected disadvantaged clusters will be identified using the Regional Cancer Screening Coordinating Centre of Occitanie (CRCDC-OC) database.

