### Data Collection and Study Variables

The study data will be generated from the CRCDC-OC database. The source of the CRCDC-OC database is the French health insurance database (*Système National des Données de Santé*; SNDS). This database contains individualized and deidentified data on all medical expenditures and reimbursements. All medical care received in the public, private, or liberal sector is recorded in the SNDS. No additional personal or clinical information will be collected during this trial. Anonymized data for each individual participant will be received, stored, and handled at International Agency for Research on Cancer (IARC) using Research Electronic Data Capture, a secure, web-based software platform designed to support data capture for research studies [29,30]. All standard precautions will be taken to ensure the privacy and protection of personal and medical information. Only the principal investigators and coinvestigators as well as the data manager will have access to the data.

This database enables access to some data on women’s characteristics (date of birth, place of residence, and type of health insurance), screening (HPV testing), and further investigations (cytology, colposcopy, biopsy, treatment of precancerous lesions, and surgery).

Real-time usage statistics generated by the chatbot platforms will be used to evaluate women’s use of the chatbot. Chat volumes, response time to women’s chat requests, the number of queries resolved, the main topics in women’s requests, navigation flow, and women’s satisfaction will be analyzed.

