### Primary Study Outcomes

The study has 2 primary outcomes: (1) the proportion of screening participation within 12 months among women recalled for CCS and (2) the proportion of HPVss-positive women who are “well-managed” as stipulated in the French guidelines. Both proportions will be compared between experimental and control groups, taking into account the stratification by age group, place of residence, and type of health insurance.

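### The covariate rules for the primary comparison disagree between two sections, and neither includes a cluster-level baseline measure of screening uptake; adding one is a cheap improvement

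*Protocol article*

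**What the plan says.** Two sections of the protocol article govern adjustment of the primary comparison.

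- Statistical Analysis: logistic models for primary and secondary outcomes, "adjusting for individual characteristics that are statistically significant in the univariate analysis and the cluster design".
- Primary Study Outcomes: both primary proportions are compared "taking into account the stratification by age group, place of residence, and type of health insurance". No significance condition is attached.

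Three other sections set the context.

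- Randomization: clusters are "randomly assigned to the 2 randomization groups in a 1:1 ratio using computer-generated simple randomization". No stratification, matching or constraint is described.
- Sample Size: a 10% precision, "which would lead to a 0.029 intracluster correlation using a beta-binomial model"; 10 clusters per arm for the overall effect, raised to 16 per arm for subgroup analyses.
- Study Population, with Data Collection and Study Variables: eligible women "have not been screened for CC for more than 4 years, and live in the disadvantaged clusters in the Occitanie Region". They are identified from the coordinating centre's (CRCDC-OC) database, of which the article says "This database enables access to some data on women’s characteristics (date of birth, place of residence, and type of health insurance), screening (HPV testing". Follow-up procedures are also recorded there.

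**The concern.** The first primary outcome is screening participation. Its natural baseline counterpart is earlier screening uptake. For an individual woman that is a constant here, because everyone eligible is a long-term non-attender. It varies only between clusters, as the share of women in each IRIS who were screened before the trial.

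A rule worded in terms of individual characteristics does not admit such a term. Allowing for the cluster design makes the standard error honest, but it does not remove variation that a baseline measure could explain. With simple allocation of 32 clusters, the design does not balance prior uptake either. At stake are some precision and the credibility of the result should the arms happen to start with visibly different uptake.

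**Working it through.** **Inputs.** From Sample Size: 15% versus 25%, m = 250 women per cluster, coefficient of variation (CV) 1.2, ICC 0.029, 80% power, two-sided 5%, subgroup alpha 2.5%/8 = 0.3125%, 16 clusters per arm. These inputs describe the composite well-managed outcome and are borrowed here for participation. The correlation r between a cluster's prior coverage and its trial outcome is not in the document. I assume 0.3, 0.5 and 0.7.

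**1. Reproducing the plan.** Under individual randomization, n per arm = [1.96·√(2·0.20·0.80) + 0.8416·√(0.15·0.85 + 0.25·0.75)]² / 0.10² = 250. For unequal clusters in a weighted analysis, DE = [1 + (m−1)·ICC] / [1 − CV²·λ(1−λ)], with λ = m·ICC/[1 + (m−1)·ICC] = 7.25/8.221 = 0.882. So DE = 8.221/(1 − 1.44·0.882·0.118) = 9.67.

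- Overall effect: 250·9.67/250 = 9.67, so 10 clusters per arm, as stated.
- At 0.3125% per tail, n = 408: 408·9.67/250 = 15.8, so 16 per arm, as stated.

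The conventional form, DE = 1 + [(CV² + 1)·m − 1]·ICC = 18.66, would need 19 per arm for the overall effect. It does not match the stated 10.

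**2. Where the variance lies.** The between-cluster share of the variance of a cluster proportion is m·ICC/(1 − ICC + m·ICC) = 7.25/8.221 = 88% at m = 250. If the abstract's roughly 4000 women are the total over 32 clusters, m = 125 and the share is 3.625/4.596 = 79%. (16·250 = 4000 suggests that the figure may instead be per arm.)

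**3. Power with the covariate.** Replace ICC by ICC·(1 − r²). Effective n per arm is 16·250/DE, and power = Φ{[0.10 − z·√(0.32/n)] / √(0.315/n)}.

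| r | Weighted DE | Power, 5% | Power, 0.3125% per tail | Conventional DE | Power, 5% |
|---|---|---|---|---|---|
| 0 | 9.67 | 95.0% | 80.7% | 18.66 | 73.7% |
| 0.3 | 9.03 | 96.2% | 84.0% | 17.07 | 77.4% |
| 0.5 | 7.88 | 97.9% | 89.6% | 14.25 | 84.4% |
| 0.7 | 6.16 | 99.5% | 96.3% | 10.01 | 94.4% |

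For the overall test the gain is 1.2 to 4.5 points with the design effect that reproduces the plan, and 3.7 to 20.7 points with the conventional one. Using t with 30 and 29 degrees of freedom and unpooled variances, the conventional column becomes 71.4%, 75.1%, 82.3% and 93.1%, so the lost degree of freedom hardly matters.

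**4. Chance imbalance.** With 16 clusters per arm, the difference in mean prior coverage has SD √(1/16 + 1/16) = 0.354 between-cluster SDs. A gap above 0.5 SD in either direction has probability 2·[1 − Φ(0.5/0.354)], about 16%. The between-cluster SD of the outcome at 20% is √(0.029·0.20·0.80) = 6.8 points. A 0.5 SD gap therefore shifts the unadjusted contrast by 0.5·r·6.8, which is 1.0, 1.7 or 2.4 points at r = 0.3, 0.5 or 0.7, against a 10-point target.

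**5. The HPVss-positive outcome.** If about 5 such women per cluster are assumed at the same ICC, the between-cluster share is 0.145/1.116 = 13%, so little can be gained there.

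**The case against.** The strongest reply is that a journal article leaves the full covariate list to the analysis plan, so the absence of one optional term is no finding. That would be decisive if the article were silent. It is not: it fixes a rule, restricts it to individual characteristics, and gives a second rule elsewhere that does not agree. The rule is open to comment, but the reply does keep the point small.

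Four stronger readings are tempting, and the document does not support them.

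- *That a univariate test is the only gateway into the model.* The Primary Study Outcomes section brings in three factors without a test. Residence might carry some area-level information, but it is undefined and is not a baseline value of the outcome.
- *That coverage per cluster is already to hand.* The article describes finding unscreened women and handling data on participants. Coverage also needs the screened, ineligible women and a denominator for each IRIS. It should be derivable from the database, but no such extraction is described.
- *That the trial loses substantial power.* The larger gains rest on a design effect that would require 19 clusters per arm, not the stated 10. The gains at 0.3125% per tail use all 32 clusters at the subgroup alpha, so they are not the power of the primary test. Because the sample consists of long-term non-attenders, general coverage may predict their response only weakly.
- *That imbalance would bias the estimate.* Under randomization a chance gap is not bias, and an analysis that respects the clustering reflects it in the confidence interval.

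**Conclusion.** The point holds as a cheap improvement. The two adjustment rules need reconciling, and neither includes a cluster-level baseline measure of uptake, although most of the variance lies between clusters and allocation is unconstrained. With r assumed between 0.3 and 0.7 and the composite outcome's inputs, the overall test gains about 1 to 5 points of power from about 95% under a design effect consistent with the plan's own counts. It gains about 4 to 21 points from about 74% if 1.2 enters the conventional design effect as a cluster-size CV. If r is near zero there is no gain. A 0.5 SD gap in prior coverage, with probability about 16%, would move the unadjusted contrast by about 1.0 to 2.4 points. This is lost precision, not bias. It concerns participation and the overall well-managed proportion; for HPVss-positive women the gain would be small.

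**What to change.** Before outcome data are seen:

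1. Reconcile the Statistical Analysis and Primary Study Outcomes sections: name the individual covariates in advance (the three factors already listed would serve) and drop selection by univariate significance.
2. In the model for participation, and for the overall well-managed proportion used for sizing, add one pre-specified cluster-level covariate: the share of women aged 30-65 in each IRIS with a recorded cervical screen before randomization. Define the look-back period, derive it as an aggregate from the CRCDC-OC database, and keep it whatever its p-value.
3. Report the model without this covariate as a sensitivity analysis.

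The cost is a wording change, one extra aggregate per cluster (the coordinating centre should confirm that it can supply both numerator and denominator), and one cluster-level degree of freedom (30 to 29). Recruitment and the number of clusters are unaffected.
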